## Methods

### Trial Design

The HELI study is a multicenter randomized controlled trial, aiming to investigate the effects of a 6-month multidomain lifestyle intervention on brain functioning and its relation with immunometabolic markers in aging. Powered to include 104 total participants, HELI has two parallel-arm treatment groups: (1) a supervised “high-intensity” coaching intervention group with weekly group meetings, lifestyle-related information and exercises, and (2) a nonsupervised “low-intensity” coaching intervention group, receiving information leaflets every 2 weeks. Because the participants of the high-intensity intervention arm were supervised in a group context, we recruited and subsequently randomized participants in 4 different inclusion waves (between May 2022 and October 2023), consisting of 19‐32 participants. Participants partook in outcome measure visits at baseline (T0) and at 6 months follow-up (T1) (see Figure 2).

The HELI study has been reviewed and accepted according to the Medical Research Involving Human Subjects Act (“Wet Medisch-wetenschappelijk Onderzoek met mensen” in Dutch) by an accredited Medical Research Ethics Committee (MREC), the MREC Oost-Nederland on December 2, 2021 (ToetsingOnline filenumber NL78263.091.21, ClinicalTrials.gov ID NCT05777863).

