**Figure 3. F3:**
[figure not shown]
Intervention overview. HUBV (Houd uw Brein Vitaal; “Keep your brain fit”) and iSLEEP are validated psychoeducational and cognitive behavioral therapy programs.

The high-intensity intervention group received a structured and personalized intervention program consisting of weekly group sessions, active guidance from an intervention supervisor, and lifestyle domain–related individual and group exercises. The low-intensity intervention group received access to general lifestyle-related health information in an individual context, provided through information leaflets sent by email once every 2 weeks. To promote intervention adherence and blinding, we adopted the FINGER-NL [108] and US POINTER approach [114] of framing both groups as lifestyle intervention recipients, instead of using the label “control group.” The groups differ in intervention structure, engagement, and intensity rather than treatment versus control.

During communication with participants, we refrained from using the terms “high-intensity” and “low-intensity” to promote group blinding as much as possible. Instead, the intervention arms were called “weekly group sessions” for the high-intensity intervention group, and “independently working on your lifestyle” for the low-intensity intervention group. An extensive description and overview of the multidomain lifestyle intervention groups is provided below and depicted in Figure 3.

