##### Group Sessions

The weekly group sessions were offered throughout the 6-month (26 weeks) intervention period. For 20 out of 26 weekly sessions, a specific lifestyle domain acted as the central theme for a given week (Figure 3). At week 1, after the baseline measurements of all participants in a wave and subsequent randomization had been concluded (T0), the intervention started off with an on-site introductory session.

The weekly group sessions provided participants with detailed lifestyle-related information, guidelines, exercises, and advice, as well as the opportunity for discussion with other group members and with the intervention supervisor. Weekly group sessions were guided by the intervention supervisor and were composed of the following recurring elements: social interaction, introductory question round, reiteration of previous lifestyle domains, dissemination, exercises, and a final question round (see Table S1 in Multimedia Appendix 1 for further details).

Over the 6-month intervention period, each of the five lifestyle domains was addressed in separate weekly group sessions (see Figure 3). We provided three distinct types of weekly group sessions:

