### Sample Size

The expected effect size for this study was determined based on other, mostly single-domain, lifestyle intervention studies with similar outcomes as our primary outcomes in the brain (eg, cerebral perfusion, working memory assessments) and in the periphery (eg, immunometabolic biomarkers, gut microbiome diversity). These studies generally found medium-to-large effect sizes (see Table S4 in Multimedia Appendix 1 [52,53,95,106,107,153-161]). Therefore, we deemed a slightly above-medium effect size of 0.30 (Cohen f[V]) suitable for our primary outcomes from baseline (T0=week 0, before start intervention) to follow-up (T1=week 26, after end intervention). The sample size calculation was performed using G*Power (version 3.1.9.6; Universität Kiel [162]). Using a multivariate ANOVA (with repeated measures and within-between interaction) *F* test with a power of 80% and a 2-tailed α-error probability of .05, we calculated that a total of 90 study participants would be required. However, based on our experience with previous fMRI and intervention studies, we expect a potential loss of data of 15% due to poor fMRI data quality (eg, motion artifacts) and potential intervention drop-outs. Therefore, to reach sufficient power, we would require a total sample size of 104 (90 participants×15% potential data loss=103.5=104) participants in this study.

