### Methods: Randomization and Blinding

Participants were randomized per inclusion wave, using stratified (2,4) block-randomization to provide a 1:1 allocation between our two intervention arms. Randomization was stratified by the factors sex (male vs female), risk factor profile (medium risk 2‐3 points vs high risk ≥4 points), and a combined factor of education level +age (70+ yearsor low education vs 60‐69 years and high education, specified as university of applied science associate degree (Dutch: HBO associate degree or higher). As with our sample size, (2,4) block-randomization was only possible with up to 3 strata, age, and education were combined in one stratification factor as they are both important covariates of cognitive functioning and aging-related cognitive decline [163].

An independent researcher from the DCCN was authorized to manually perform the randomization. This authorized researcher had no affiliation with the project and therefore had no bias in the allocation procedure.

Given the nature of the intervention arms, the participants and intervention supervisor were unable to remain blinded to the assignment to the intervention arms. Researchers conducting the follow-up outcome measure visits remained blinded and unaware of the intervention arm allocation. Only in case of unforeseen circumstances would deviations be made (eg, an unblinded researcher conducting the MRI protocol). Neuropsychological tests and task trainings (ie, n-back task) were conducted by a blinded researcher in all cases. Participants were asked to refrain from speaking about the intervention contents and experience during the follow-up outcome measure visits to prevent accidental unblinding.

The requirement for emergency unblinding was not applicable to this study, as participants were unblinded to the group allocation and the nature of the study setting.

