### Methods: Statistics and Analysis

We will test for change between T0 and T1 in the primary and secondary outcome variables, both within-group and between-group, using linear mixed-effect models with random effects for intercept (individuals). The intervention group and time will be included as fixed effects, as well as the interaction term between intervention group and time, to model the difference in change between T0 and T1 as a function of group allocation.

In addition, we will test for correlations in change (T0 minus T1) between (primary) brain outcomes and (primary) peripheral outcomes. We will select an appropriate correlation test for our data, based on whether assumptions are met. We will include both the high- and low-intensity groups if there is enough variance in change across both groups; else, we will only include the high-intensity group.

The level of significance will be set at 0.05 (2-sided). FDR correction will be used to account for multiple comparisons of secondary and exploratory outcomes. FWE correction will be used for secondary whole-brain analyses.

As part of exploratory analyses to assess the domain-specific effects on our primary outcome measures, we will take the pre- and posteffects of the primary outcome measures and use domain-related questionnaire scores and smartwatch-derived physiological data as a measure of improvement for each respective domain as predictors in linear mixed-effect models.

We will perform an intention-to-treat analysis. Participants who withdrew from the study during the 6-month intervention period, but had not withdrawn consent, were invited to the T1 (after week 26) follow-up outcome assessments. This means that we will use all available collected data, including collected (follow-up) data of participants who dropped out of the intervention. Missing data or data with insufficient quality, however, will not be used in the analysis.

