We ultimately managed to include a total of 102 participants within our study. Our study population shares a similar baseline lifestyle modifiable risk factor profile (CAIDE) compared with the FINGER study, based on the total number of participants with hypertension, hypercholesterolemia, and diabetes (see Table S5 in Multimedia Appendix 1 [165-167]). Other previous multidomain lifestyle intervention studies in older adults, such as the pre-DIVA, MAPT, and J-MINT studies, used inclusion criteria different from the CAIDE-related lifestyle modifiable risk factors, or included participants solely based on age. Compared with previous studies, our study population is relatively highly educated, and we were unable to include a comparable number of participants with a lower education level. However, many of these earlier studies completed participant inclusion over a decade ago, and education levels have generally increased over time, which may reflect cohort effects. Because education level is often used as a covariate in task-related neuroimaging outcomes and neuropsychological test data, this is an important limitation to consider during data interpretation and comparison of results with other studies. For a more detailed description of the baseline characteristic comparison between the HELI study and previous multidomain lifestyle intervention studies, see Table S5 in Multimedia Appendix 1.

To summarize, the most important strength of the HELI study is its unique combination of multimodal neuroimaging and peripheral phenotyping with a multidomain lifestyle intervention. Moreover, the study has several additional strengths. First, the design has two active arms, which promote blinding and intervention adherence, while preserving between-group comparisons of lifestyle interventions. Second, the group approach within the high-intensity group is a strength, as it encourages peer support and intervention adherence. Finally, the online-onsite combination establishes a future-oriented intervention framework that ensures both quality and broad applicability. Limitations of the study comprise the limited number of objective domain-specific adherence measures and the selection bias toward more highly educated individuals, potentially due to the digital intervention format.

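### The high-intensity arm is treated in session groups but the stated model has only a participant random effect, so the group×time standard error is too small for any outcome whose change clusters by group

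*Protocol article*

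**What the plan says.** **Delivery.** Trial Design explains the waves by the group format: because "participants of the high-intensity intervention arm were supervised in a group context, we recruited and subsequently randomized participants in 4 different inclusion waves". Group Sessions describes what happens there: "Weekly group sessions were guided by the intervention supervisor and were composed of the following recurring elements: social interaction, introductory question round". The Discussion (Principal Findings) counts this as an advantage: "the group approach within the high-intensity group is a strength, as it encourages peer support and intervention adherence". The low-intensity arm, in the text under Figure 3, "received access to general lifestyle-related health information in an individual context".

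**Randomization.** The unit is the individual, within wave: "Participants were randomized per inclusion wave" (Methods: Randomization and Blinding). Session groups therefore form after randomization, and in one arm only.

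**Analysis.** Methods: Statistics and Analysis plans to test change "using linear mixed-effect models with random effects for intercept (individuals"). The fixed part is also given: "The intervention group and time will be included as fixed effects, as well as the interaction term between intervention group and time". No term for wave or session group appears.

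**Sample size.** Sample Size uses 80% power, two-sided alpha 0.05 and this planning effect: "we deemed a slightly above-medium effect size of 0.30 (Cohen f[V]) suitable for our primary outcomes". It arrives at 90 evaluable participants, raised to 104 for 15% data loss. No ICC or design effect enters.

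**The concern.** This is a partially nested design. High-intensity participants meet weekly, discuss and exercise together, and are meant to influence one another. Low-intensity participants have no such grouping. If members of a session group change alike, 53 high-intensity participants carry less information than 53 independent people.

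The individual random intercept does not help. It accounts for the two visits of one person, not for similarity in change between people in the same group. The omitted variance would make the interval for the group×time effect too narrow and the nominal 5% test too liberal, and the planned power would not be reached.

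The article writes out the random-effects structure, so the point is about what is stated, not about detail left to a fuller document.

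**Working it through.** **Inputs from the article.** f(V) = 0.30, 80% power, two-sided alpha 0.05, N = 90 and 15% loss (Sample Size); 53 high-intensity and 49 low-intensity participants randomized (Results); 4 waves of 19 to 32 people (Trial Design).

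**Assumptions.** ICC of change 0.01, 0.05 or 0.10; one or two session groups per wave; equal group sizes; normal approximation. Half of a wave is about 10 to 16 people, which fits one group per wave but does not establish it.

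**Step 1: reproduce the plan's figure.** For two groups and two visits, the interaction F test has 1 and N − 2 degrees of freedom and noncentrality λ = 0.30² × N. At N = 90, λ = 8.1 and power is 0.804; at N = 89 it is 0.799. So 90 is reproduced exactly under full independence and holds no allowance for clustering. With two groups, f = 0.30 corresponds to d = 2 × 0.30 = 0.60 on the change score.

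**Step 2: baseline without clustering.** With two visits and complete data, group×time is a comparison of mean change. After 15% loss, n_H = 53 × 0.85 = 45.05 and n_L = 49 × 0.85 = 41.65. In SD units of change:

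V0 = 1/45.05 + 1/41.65 = 0.0462; SE = 0.215; power = Φ(0.6/0.215 − 1.96) = 0.80.

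**Step 3: cluster the high-intensity arm only.** With m members per group:

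- design effect DE = 1 + (m − 1) × ICC
- V = DE/n_H + 1/n_L
- SE ratio (true/model) = √(V/V0)
- alpha = 2 × [1 − Φ(1.96/SE ratio)]
- power = Φ(0.6/√V − 1.96)

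| Groups per wave | m | ICC | DE | V | SE ratio | Alpha | Power |
|---|---|---|---|---|---|---|---|
| one | 45.05/4 = 11.26 | 0.01 | 1.10 | 0.0485 | 1.02 | 5.6% | 0.78 |
| one | 11.26 | 0.05 | 1.51 | 0.0576 | 1.12 | 7.9% | 0.71 |
| one | 11.26 | 0.10 | 2.03 | 0.0690 | 1.22 | 10.9% | 0.63 |
| two | 45.05/8 = 5.63 | 0.01 | 1.05 | 0.0472 | 1.01 | 5.3% | 0.79 |
| two | 5.63 | 0.05 | 1.23 | 0.0514 | 1.05 | 6.3% | 0.75 |
| two | 5.63 | 0.10 | 1.46 | 0.0565 | 1.11 | 7.6% | 0.71 |

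At ICC 0, DE = 1 and nothing changes.

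**Step 4: check by simulation.** With 40,000 trials per ICC, four high-intensity groups and no data loss (m = 53/4 = 13.25), simulated alpha was 0.054, 0.085 and 0.119, against 0.057, 0.085 and 0.120 from the formula.

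**Step 5: shared wave effects.** With a wave variance of 0.05 common to both arms and no arm-specific clustering, simulated alpha was 0.045. Omitting wave is then slightly conservative, so the problem is confined to group effects in the high-intensity arm, and a wave fixed effect alone would not solve it.

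**The case against.** **The size is not known.** This stands. No ICC and no number of groups per wave is given. At ICC 0.01 the effect is negligible, and smaller groups weaken it further.

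**Not every outcome need cluster.** A reader might infer that alpha exceeds 5% for all outcomes. The article does not support that. It says the group format promotes peer support and adherence; it does not say that changes in hippocampal perfusion, TNF-α or Chao1 are correlated within groups. The point holds only for outcomes with positive within-group correlation of change.

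**Which null hypothesis?** Individuals were randomized within wave. If the intervention changes nobody's outcome, sitting in a group cannot create arm-specific clustering, and the test is not inflated by it. The alphas above apply where group-specific effects exist but average to zero. This is a real restriction.

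**Features that limit clustering.** All groups follow a common programme, and 90 of the expected 180 weekly minutes lie outside the sessions. The article speaks of the intervention supervisor in the singular. If one person led every group, a supervisor effect is confounded with arm and is not between-group variance, so it adds nothing to this argument.

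**Too few clusters, and sensitivity analyses belong in a fuller document.** About four clusters do estimate the variance poorly, which is a reason not to replace the primary model. But the model as stated assumes independence in an arm designed around interaction, and that can be judged from the article alone.

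**Conclusion.** The concern holds in conditional form. For any outcome whose change correlates within high-intensity session groups, the stated model gives too small a group×time standard error, and the sample size makes no allowance for it.

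Under one group per wave, 15% loss and ICC 0.01 to 0.10, the true standard error is 2% to 22% larger than the model's; put the other way, the model's is 2% to 18% too small. Alpha runs from 5.6% to 10.9% and power from 0.78 down to 0.63. With two groups per wave the ranges are 5.3% to 7.6% and 0.79 to 0.71. The ICC and the groups per wave are assumptions throughout.

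A reader might go further and conclude that the primary model is invalid or that the trial's 5% level is broken. The documents do not support that: nothing in them shows that the ICC is above zero for any primary outcome.

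**What to change.** Keep the primary model. Before unblinded results are examined, name one sensitivity analysis for the primary outcomes: a session-group random effect on change (entering at T1) in the high-intensity arm only, with small-sample degrees of freedom. State how many session groups ran in each wave and their sizes.

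Because about four clusters estimate that variance poorly, also report the primary confidence intervals multiplied by the SE ratio over a stated ICC range such as 0.01, 0.05 and 0.10, using the actual group sizes. Say for each primary claim whether it holds across that range.

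The cost is analysis time. Group meeting attendance is already collected (Other Study Parameters), and no new data or design change is needed. The downside is wider intervals and few cluster degrees of freedom. At the planned 45 per arm in four groups, power with small-sample degrees of freedom is about 0.74 at ICC 0 and 0.71, 0.61 and 0.51 at ICC 0.01, 0.05 and 0.10. This is why the analysis should sit beside the primary model and not replace it.

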**Figure 2. F2:**
[figure not shown]
Overview of the study design. Schematic overview of study visits, assessments, and intervention groups. Before **T0 **and after **T1,** the intervention period of 6 months, participants visited the Donders Center for Cognitive Neuroimaging (DCCN) and Wageningen University and Research (WUR) study centers with one week in between.

### Methods: Participants, Interventions, and Outcomes

#### Study Setting

The HELI intervention is based on the FINGER-NL lifestyle intervention, a multicenter, randomized, controlled, multidomain lifestyle intervention effectiveness trial in the Netherlands. The rationale and study design of FINGER-NL have been published previously [108]. Both HELI and FINGER-NL are part of the overarching Maintaining Optimal Cognitive Functioning In Aging (MOCIA) research program [109], and follow an inclusion procedure with similar lifestyle modifiable risk factor inclusion criteria as the FINGER study [18,110]. The HELI study is conducted at two separate research centers in the Netherlands, namely the Donders Institute for Brain, Cognition and Behavior, Center for Cognitive Neuroimaging (DCCN; Radboud University, Nijmegen, the Netherlands), and the Division of Human Nutrition and Health at Wageningen University and Research (WUR, Wageningen, the Netherlands). Study visits were performed at both centers, but inclusion, screening, randomization, guidance of the intervention, and monitoring were performed by the DCCN.

#### Recruitment

To achieve adequate participant enrollment and reach the target sample size of 104 included participants, we have used an array of recruitment methods. Our primary sources of enrollments came from: (1) recruitment advertising on Facebook; (2) WUR and DCCN research center participant databases; (3) newsletters of Dutch brain research institutions and associations (eg, Netherlands Brain Foundation and Alzheimer Association Netherlands); (4) messages on WUR and DCCN research center websites and social media channels; (5) articles and recruitment dissemination via flyers, and in local newspapers, radio station, and television broadcast; and (6) word of mouth.

### Eligibility Criteria

#### Inclusion Criteria

Individuals had to meet the following inclusion criteria to be eligible to participate in this study:

Aged between 60‐75 years (at the moment of signing written informed consent);Fluency in Dutch (speaking, reading, and writing);Willing to travel to the partaking research centers in Nijmegen and Wageningen (to ensure study center visits are plausible without excessive travel burden);Score ≥2 points on the self-reported “Modifiable cardiovascular risk factor scale” (see Table 1 below), indicating a presently increased risk for cognitive decline based on risk factors which are modifiable by lifestyle changes (adapted from Cardiovascular Risk Factors, Aging, and Incidence of Dementia [CAIDE] [111]).

**Table 1. T1:** Modifiable cardiovascular risk factor scale.

Risk factor	Points
BMI ≥25 kg/m^2^ (overweight or obesity)	1
Physical inactivity (below the 2020 WHO guidelines [112]:<300 minutes of moderate intensity aerobic physical activity, or <150 minutes of vigorous intensity aerobic physical activity per week, spread out over several days)	1
Hypertension (systolic blood pressure ≥140 mmHg, and diastolic blood pressure ≥90 mm Hg)	1 (2 points are assigned if hypertension is not being actively treated with antihypertensive medication, given the increased cardiovascular burden)
Hypercholesterolemia (total cholesterol >5 mmol/L, or LDL-cholesterol >3 mmol/L)	1
Diabetes type II	1
Mild cardiovascular disease (eg, intermittent claudication, varicose veins; In contrast, moderate or severe cardiovascular disease such as stroke, angina pectoris, heart failure, myocardial infarction, or revascularization surgery in the last 12 months before pre-screening are exclusion criteria as described below under section “Exclusion criteria”)	1

